## Abstract

**Background:**

Atrial fibrillation is a common cause of stroke and other morbidity. Adequate treatment with anticoagulants reduces the risk of stroke by 60 %. Early detection and treatment of atrial fibrillation could prevent strokes. Atrial fibrillation is often asymptomatic and/or paroxysmal.

Case-finding with pulse palpation is an effective screening method, but new methods for detecting atrial fibrillation have been developed. To detect paroxysmal atrial fibrillation ambulatory rhythm recording is needed.

This study aims to determine the yield of case-finding for atrial fibrillation in primary care patients. In addition, it will determine the diagnostic accuracy of three different case-finding methods.

**Methods/Design:**

In a multicenter cluster randomised controlled trial, we compare an enhanced protocol for case-finding of atrial fibrillation with usual care. We recruit 96 practices. We include primary care patients aged 65 years or older not diagnosed with atrial fibrillation. Within each practice, a cluster of 200 patients is randomly selected and marked. Practices are evenly randomised to intervention or control group. The allocation is not blinded.

When a marked patient visits an intervention practice, the case-finding protocol starts, consisting of: pulse palpation, sphygmomanometer with automated atrial fibrillation detection and handheld single-lead electrocardiogram (ECG). All patients with at least 1 positive test and a random sample of patients with negative tests receive a 12-lead ECG. Patients without atrial fibrillation on the 12-lead ECG, undergo additional continuous Holter and use the handheld single-lead ECG at home for 2 weeks.

Control practices provide care as usual.

The study runs for 1 year in each cluster. The primary outcomes are the difference in detection rate of new AF between intervention and control practices and the accuracy of three index tests to diagnose AF. We are currently recruiting practices.

The ‘Detecting and Diagnosing Atrial Fibrillation’ (D_2_AF) study will determine the yield of an intensive case-finding strategy and the diagnostic accuracy of three index tests to diagnose atrial fibrillation in a primary care setting.

**Trial registration:**

Netherlands Trial Register: NTR4914, registered on the 25 of November 2014.

## Background

Atrial fibrillation (AF) is a common cardiac arrhythmia, associated with substantial health risks. AF increases mortality, reduces the quality of life and increases the risk of heart failure. Moreover, AF is an important risk factor for stroke. Prevalence of AF increases with age, from 1 % in the general population up to 7–8 % in people over 65 years old [1, 2]. With increasing age, patients also have a higher risk of stroke [3]. Up to 30 % of ischemic strokes are AF-related [4–6]. Treatment with oral anticoagulants reduces the risk of stroke by 60 % [7, 8]. However, in nearly a quarter of patients with stroke AF is detected after this event [9]. If we can detect AF before a stroke occurs and start anticoagulant therapy when appropriate, we may be able to prevent more than half of AF-related strokes [4, 6, 9–11].

Although AF can be a symptomatic condition with patients experiencing palpitations, exercise intolerance or fatigue, AF often is asymptomatic [12] and remains undetected. Furthermore, patients can have recurrent intermittent episodes of AF, paroxysmal AF (pAF). As with persistent AF, the risk of stroke is substantially increased in patients with pAF [13, 14]. Therefore, detecting pAF is as important as detecting persistent AF, but more challenging.

To establish the diagnosis of AF, an electrocardiogram (ECG) recording – either on a regular 12-lead ECG or a 30-second rhythm strip – has to be made showing irregular RR intervals without distinct P waves. When used as screening tools, ECG and ambulatory rhythm recording are costly and time-consuming. Case-finding in general practice using pulse palpation, improved the detection of AF compared with care as usual (incidence of AF 1.63 % versus 1.04 %, difference 0.59 %, 95 % CI 0.20 % to 0.98 %) [15]. Opportunistic screening in patients aged 65 years and over was as effective as systematic screening but at lower costs [15].

Recently, new methods for detecting AF have been developed [16]. One development is the equipment of automatic sphygmomanometers with an algorithm for irregular beat detection (eBPM-AF). The National Institute for Health and Clinical Excellence (NICE) guideline advocates the use of one of these devices, i.e. the Microlife® WatchBP Home A device [17]. Other methods use a single-lead ECG. The MyDiagnostick (Applied Biomedical Systems® (ABS), Maastricht, The Netherlands) is an example of a handheld ECG device, which records a single-lead ECG (left-right arm) [18].

To detect cases of pAF, ambulatory rhythm recording is needed [19]. Traditionally, either 24-hour Holter or event recording is used. In post-stroke patients, a 30-day period of automatically triggered event recording increased the detection rate of pAF 5-fold compared with a 24-hour Holter (detection rate of 16.1 % versus 3.2 %) [20]. In primary care patients with palpitations, monitoring for 14 days diagnosed about 80 % of relevant arrhythmias [19].

New developments have enabled the use of continuous ECG registrations for longer periods (continuous Holter) and make loop recording unnecessary. In general, ambulatory rhythm recording is used in symptomatic patients or as part of follow-up after stroke. There is insufficient evidence about the effectiveness of ambulatory rhythm registration for the detection of AF in asymptomatic patients (in general practice). This is a major evidence gap and further research is recommended [21, 22].

The ‘Detecting and Diagnosing Atrial Fibrillation’ (D_2_AF) study investigates whether enhanced opportunistic case-finding – using pulse palpation, single-lead handheld ECG and eBPM-AF – increases detection of AF in general practice patients of 65 years and over. Additionally, the study determines the most effective method of case-finding by comparing the diagnostic yield of pulse palpitation, handheld ECG and eBPM-AF alone and in combination.

## Methods

### Design

We perform a multicenter cluster randomised controlled trial (RCT) comparing enhanced case-finding of AF with usual care. In each practice, the study runs for 1 year. In the intervention arm, we run a diagnostic study comparing 3 different methods for case-finding of AF with a composite reference standard consisting of a 12-lead ECG and a 2 week Holter. This way, we determine the yield of each method individually and combined to detect unknown AF. Figure 1 shows a flowchart of the study design.

**Fig. 1 Fig1:**
[figure not shown]
Study design of ‘Detecting and Diagnosing Atrial Fibrillation’ D_2_AF. GP, general practitioner; hand-ECG, handheld ECG device; eBPM-AF, automatic sphygmomanometer with an algorithm for irregular beat detection; ECG, electrocardiogram

### Ethics

The D_2_AF study proposal was approved by the medical ethical board of the Academic Medical Center in Amsterdam (dated 14 November 2014, number NL48215.018.14). The D_2_AF study is registered at The Netherlands Trial Register (NTR number NTR4914).

### Participants: practices and patients

General practices are recruited across The Netherlands. We regard two or more general practices sharing facilities as one practice. Within each practice, we form one cluster by selecting a random fixed sample of two hundred patients out of the eligible patients.

The inclusion criterion for selection of the cohort is an age of 65 years and over; the exclusion criterion is previously documented AF. Additional criteria are applied only to patients in the intervention group for whom case-finding would be inappropriate (see intervention practices). After selection of the study cohort, we extract the medical files to determine the baseline characteristics (e.g. age, sex and medical history including heart disease, hypertension, previous stroke/transient ischaemic attack (TIA), diabetes).

All data are entered into our secured trial management system. This system also gathers all other data during the study. Investigators enter data directly into the system using electronic case record forms (eCRF).

### Cluster randomisation

Clusters are evenly allocated to either the intervention or the control group using stratified randomisation. To stratify clusters, we determine the prevalence of AF in all patients aged 65 years and over in participating clusters using International Classification of Primary Care (ICPC)-codes in the medical files. Subsequently, we stratify clusters in high-prevalence and low-prevalence clusters. As a cut-off we use the average prevalence of AF in the associated general practices of the 2 universities involved in this study: 8.05 %. We use computerised randomisation in permuted blocks of random sizes. After randomisation, the investigator informs the participating practices of the allocation.

### Intervention practices

In each practice, the selected 200 patients are marked in the medical records of the practice before the start of the study. When a marked patient makes an appointment for a consultation at the practice we ask him or her to participate. The sub-investigator (practice nurse, practice assistant or general practitioner) does not carry out the intervention in patients not suited for case-finding based on the following criteria:having a pacemaker or implantable cardioverter-defibrillator (ICD)legal incompetence or inability to give informed consentsuffering from a terminal illness (as defined by the general practitioner)inability to come to the practice to participate in the diagnostic process; for instance, a patient who is chronically bedridden. Patients who cannot visit the practice due to a temporary situation (such as the flu) are not excluded

The reason is noted in the trial management system. All patients who undergo the case-finding protocol in the intervention group will be asked written informed consent. We do not ask informed consent in the control group since we merely analyse these patients on a group level. They receive care as usual and we do not want to trigger additional awareness of AF.

#### Diagnostic tests

The sub-investigator collects the baseline information on the patient history, weight, length and current symptoms indicative of AF. Subsequently, the sub-investigator performs the following three index tests in all study patients:

*Pulse palpation*: manual palpation of the radial artery in the wrist with the fingertips for a minimum of 15 seconds. The frequency is registered. The heart rhythm is classified as ‘regular’, ‘one to three skipped or extra beats’ or ‘irregular’. Both ‘one to three skipped or extra beats’ and ‘irregular’ are regarded as a positive result. The filling pressure is classified as ‘equal’ or ‘unequal’.

*eBPM-AF*: the WatchBP Home A (Microlife®, Widnau, Switzerland) is an electronic sphygmomanometer with an algorithm for irregular beat detection. The algorithm calculates the irregularity index based on the interval time between heartbeats and indicates an irregular pulse if the threshold is exceeded. A cuff is applied around the patient’s left or right upper arm. The cuff inflates and deflates automatically after pressing the ‘ON’ button. The display shows the average of three blood pressure measurements. If an irregular pulse is detected in at least two out of three measurements, an icon on the display saying ‘Afib’ starts blinking [17]. If the device is not able to correctly analyse the rhythm this is noted in the eCRF.

*Handheld ECG at the practice*: the MyDiagnostick (ABS, Maastricht, The Netherlands) is a 24-cm long bar with metallic electrodes at both ends. It records a single-lead ECG (left-right arm). The device switches on automatically when holding it with both hands. An automatic algorithm calculates a rhythm-score, periodicity-score and variability-score based on computed intervals between two R waves. If the threshold is exceeded, a red light indicates possible AF. The outcome of the handheld ECG is noted in the eCRF. If the device cannot make a recording this is registered. Recordings are stored locally and are uploaded as a PDF in the local PC application [23].

The order in which the index tests are performed is set. Pulse palpation is performed and recorded first. Then, by an alternating pre-set order in the eCRF, both eBPM-AF and handheld ECG are performed and recorded.

All patients scoring positive on at least 1 of the 3 index tests will receive a 12-lead ECG in the same session as the index tests. To calculate sensitivity and specificity of the screening procedure, a random sample of 10 % of patients who score negative on all 3 index tests also receive a 12-lead ECG. An overview of these procedures can also be seen in Fig. 1. The sub-investigator is blinded to the ECG results while performing the index tests.

12-lead ECG: the 12-lead ECG device (Fysiologic®, Amsterdam, The Netherlands) is paperless and does not display the ECG. The ECG is transferred digitally and assessed by an experienced assessor, supervised by a cardiologist. In case the ECG shows any serious clinically relevant abnormality, the general practitioner (GP) is notified immediately. A second cardiologist re-assesses all AF-diagnosed ECGs and a random sample of negative ECGs. Both cardiologists are provided with basic data such as age and gender but are blinded to all previous measurements. Any disagreement on diagnosis is solved by a third cardiologist. AF is defined as the absence of distinct P waves and a completely irregular RR interval [24].

If a patient is diagnosed with AF, the study protocol is finished. Results of the ECG are reported back to the GP, who provides care at his discretion.

In patients in whom no AF is diagnosed on a 12-lead ECG, 2 additional tests are performed to detect pAF:Handheld ECG at home: the same device (MyDiagnostick, ABS, Maastricht, The Netherlands) as mentioned above is used, but the indication light is set off. Thus, the patient is blinded for the results of the test (light will not blink). The patient is instructed to use the handheld ECG three times a day at set times. After 2 weeks of recording, data are uploaded as PDF in the local PC-application. The MyDiagnostick can store up to 140 ECG strips.Two-week Holter: the same device (Fysiologic®, Amsterdam, The Netherlands) as for the 12-lead ECG is used. The wiring has four different patches instead of ten. With these 4 patches, leads V1 and V5 are obtained. The patient receives a small disposable shoulder bag to wear the device and several sets of patches with instructions so they can change them. After 2 weeks of continuous recording, data are transferred and assessed by an experienced assessor, supervised by a cardiologist. The number and duration of AF episodes are registered. In case the ECG shows any serious clinically relevant abnormalities, the GP is notified immediately. A second cardiologist, blinded to previous assessments re-assesses all AF-diagnosed Holters. Furthermore, a random sample of negative Holters is re-assessed. We define AF as any arrhythmia that has the characteristics of AF (see above) and lasts at least 30 seconds [24].

#### Diagnoses ‘atrial fibrillation’

To diagnose AF, we use a composite reference standard consisting of the results of the 12-lead ECG and the 2-week Holter as defined previously.

Besides cases found with our case-finding protocol, we will also perform computer searches of the medical records to identify all new cases of AF. We ask the sub-investigator to report how the diagnosis was established in new cases of AF not detected with the intervention.

#### Quality of life

Little is known of the quality of life of asymptomatic AF patients. To investigate this, we use the EuroQol 5D (EQ-5D) questionnaire to measure quality of life. EQ-5D is a generic tool that assesses five dimensions of health-related quality of life by use of a questionnaire and a visual analogue scale [25]. We opt for 1000 patients in the intervention practices to participate: all patients with newly diagnosed AF saturated with a random sample of patients not diagnosed with AF. The reason for the visit may affect quality of life at the time of the visit. Therefore, we delay the timing of the questionnaire until the end of the study year.

### Control practices

In each practice, the selected 200 patients are marked in the medical records of the practice before the start of the study, but the marking is blinded to the sub-investigators. Neither the sub-investigators nor the patients are aware of participation in the study. The control practices perform ‘usual care’ at the discretion of the GP. Currently, the guideline on AF of the Dutch College of General Practitioners does not recommend screening for AF. Pulse palpation is not carried out systematically.

At the end of the study year, we perform computer searches of the medical records to identify all new cases of AF in the control practices. We evaluate the route that led to the diagnosis of AF. To that end, we will study the patients’ files to determine the path by which the diagnosis AF is made.

### End of the study

The study ends when all clusters have finished their 1-year study period.

### Outcome measures

#### Primary outcome measures

The yield of a case-finding strategy for AF (including paroxysmal and asymptomatic AF) compared with care as usual.The diagnostic accuracy (sensitivity and specificity) of each of the three index tests (pulse palpation, eBPM-AF and handheld ECG) to diagnose AF and the accuracy of various combinations of case-finding strategies with the results of the 12-lead ECG and 2-week Holter as reference standard.

### Secondary outcome measures

The incidence and prevalence of AF (including paroxysmal and asymptomatic) in patients aged 65 years and over in Dutch general practice.The diagnostic accuracy (sensitivity and specificity) of the handheld ECG at home to detect pAF with the 2-weeks Holter as the reference standard.The quality of life of patients with newly detected asymptomatic AF compared with healthy controls as measured with the EQ-5D.

### Sample size calculation

The primary outcome is the difference in the detection rate of new AF in 1 year between intervention and control practices. We estimate that the yearly incidence of new AF in the Netherlands in patients aged 65 and over is 1.3 % and assume that this is the detection rate in control practices [26]. In previous research among a similar group of patients the odds ratio (OR) of newly identified AF by opportunistic screening compared with no screening in the control group was 1.61 (95 % CI 1.14–2.29) [15]. In that study, ECG was offered if the pulse of the patient was irregular. Since we will provide a more extensive diagnostic programme of various diagnostic methods, it is likely that we will find a higher detection rate of (paroxysmal and asymptomatic) AF. We assume that an OR of 1.8 is reasonable. The detection rate in the intervention group is estimated at 2.32 % [27]. To detect an absolute difference of 1.02 % in the detection rate of new cases of AF between the intervention and control arm of the study with 80 % power at a significance level of 5 %, we will need 2701 patients in each group [28]. Outcomes for individuals within clusters may be correlated as we will randomise practices (i.e. clusters). To take into account the effect of cluster randomisation we calculate a design effect of 2.99 based on fixed cluster sizes of 200 patients and an intracluster correlation coefficient (ICC) of 0.01 [29, 30]. In a study comparable to ours, an ICC of 0.0027 between practices was found at the end of the study [15]. Increasing the sample size by a design effect of 2.99 the number of required inclusions becomes 8076 patients per group. Additionally, we take into account a loss to follow-up of 15 %. After correcting for loss to follow-up we get a total of 9501 patients. We decided on 48 even cluster sizes of 200 patients which makes a total of 9600 patients. Our sample size and study design are comparable to the study by Hobbs et al. [22].

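### The sample size section labels the per-group figures 9501 and 9600 as totals, so it states half the planned trial size; the 96 planned practices do meet the stated power

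*Protocol article*

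**What the plan says.** The Sample size calculation section builds the number in steps.

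- It takes a yearly incidence of new AF that "in patients aged 65 and over is 1.3 % and assume that this is the detection rate in control practices", then an odds ratio: "We assume that an OR of 1.8 is reasonable". From these, "The detection rate in the intervention group is estimated at 2.32" %.
- At 80 % power and 5 % significance it needs 2701 patients in each group.
- A design effect of 2.99 (200 patients per cluster, ICC 0.01) raises this: "the number of required inclusions becomes 8076 patients per group".
- After a 15 % allowance for loss to follow-up, "we get a total of 9501 patients".
- This is rounded up to 48 clusters of 200, "which makes a total of 9600 patients".

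The Abstract (Methods/Design) says "We recruit 96 practices", with 200 patients selected in each and practices split evenly between the two arms.

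**The concern.** The first two patient numbers are labelled per group and the next two are labelled as totals, yet no doubling or halving comes between them. Taken at its word, a total of 9501 leaves about 4750 patients per group (9501/2), well under the 8076 per group required one sentence earlier. The final figure also conflicts with the Abstract: 48 clusters and 9600 patients as the whole trial, against 96 practices of 200.

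The sample size section is where a reader looks for the planned size and for what supports the 80 % power claim. With 9600 on record as the total, a trial that includes 19,200 patients would appear to have doubled without explanation. One that stopped at 48 practices would appear complete.

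**Working it through.** **Inputs.** All are from the Sample size calculation section except the last. Control rate 1.3 %; odds ratio 1.8; intervention rate 2.32 %; 80 % power; 5 % significance (sidedness not stated; two-sided reproduces the plan's figure); cluster size 200; ICC 0.01; loss 15 %. From the Abstract: 96 practices, 200 patients each, even allocation.

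**Reproducing the plan's chain**

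1. Intervention rate: odds = 1.8 × 0.013/0.987 = 0.02371, so p = 0.02371/1.02371 = 2.316 %, stated as 2.32 %.
2. Unadjusted n per group, pooled two-proportion formula without continuity correction: n = [1.96·√(2p̄(1−p̄)) + 0.842·√(p₁(1−p₁) + p₂(1−p₂))]² / (p₂−p₁)². This gives 2699 with 2.316 % and 2681 with the rounded 2.32 %. The plan has 2701, so the figure reproduces as a **per-group** number.
3. Design effect: 1 + (200 − 1) × 0.01 = 2.99.
4. 2701 × 2.99 = 8076 **per group**.
5. 8076/0.85 = 9501.2. The plan's 9501 is therefore a **per-group** number.
6. 9501/200 = 47.5, rounded up to 48 clusters **per group**; 48 × 200 = 9600 **per group**.
7. Whole trial: 2 × 48 = 96 clusters, and 96 × 200 = 19,200 patients. The 96 agrees with the Abstract.

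Every magnitude reproduces. Only the word total at steps 5 and 6 does not.

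**Power under the two readings.** Effective n per group = (patients retained)/(design effect), put through the same formula with 1.3 % against 2.32 %. The design effect is either kept at 2.99 or recalculated for the 170 patients retained per cluster: 1 + 169 × 0.01 = 2.69. For ICC 0.0027 the corresponding values are 1 + 199 × 0.0027 = 1.537 and 1 + 169 × 0.0027 = 1.456.

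| Reading | ICC | Loss | Effective n per group | Power |
|---|---|---|---|---|
| 9600 per group (48 practices) | 0.01 | 15 % | 8160/2.99 = 2729 | 80.7 % |
| same | 0.01 | 15 % | 8160/2.69 = 3033 | 84.6 % |
| same | 0.01 | none | 9600/2.99 = 3211 | 86.6 % |
| 9600 in total (24 practices per group) | 0.01 | 15 % | 4080/2.99 = 1365 | 51.5 % |
| same | 0.01 | 15 % | 4080/2.69 = 1517 | 55.9 % |
| same | 0.01 | none | 4800/2.99 = 1605 | 58.2 % |
| same | 0.0027 | 15 % | 4080/1.537 = 2654 | 79.6 % |
| same | 0.0027 | 15 % | 4080/1.456 = 2802 | 81.7 % |

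With 2.316 % in place of 2.32 %, the 48-practice figures after loss are 80.4 and 84.4 %, so rounding does not matter. At the planning ICC, only the per-group reading delivers the stated 80 %.

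**The case against.** The intended meaning can be recovered. The Abstract gives both factors of the true total, 96 practices and 200 patients each, with even allocation, so 9600 per group is the only size consistent with it. The sample size section also points that way: 9501 cannot be a two-group total when 8076 per group (16,152 in all) has just been required. The authors probably meant the final number after all corrections and dropped the unit. Practices are what is recruited and randomised, and the 200 patients are a fixed sample drawn from the records, so progress is naturally counted against 96. The primary analysis takes all patients in the clusters as its denominator and does not use the 9600.

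This stands as an account of the consequences. It does not make the sentence right: the two preceding figures carry a per-group label, so the change to a total reads as a change to the whole trial, and 19,200 is printed nowhere in the article.

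A reader might go further and infer that the trial is planned at half the size it needs, with power near 50 %. The documents do not support that. No section plans 24 practices per group, and the 96 practices that are planned meet the power target. Even for the literal reading the shortfall is conditional on the planning ICC of 0.01. At the 0.0027 that the section quotes from a comparable study, 9600 in total would reach about 79 to 82 % after loss. Since the calculation was made at 0.01, this does not rescue the label.

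**Conclusion.** The point holds as a reporting error. The numbers 9501 and 9600 (48 clusters) are per-group figures called totals, and the sample size section thereby states half the planned trial: 9600 instead of 19,200. It contradicts both its own preceding step and the Abstract.

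The design itself is adequately sized on the plan's own assumptions (1.3 % against 2.32 %, ICC 0.01, 15 % loss, two-sided 5 %), with about 80 to 85 % power from 48 practices per group. The range reflects whether the design effect is recalculated for the smaller retained clusters. The importance is low: no estimate, analysis or allocation depends on the mislabelled figure. It is still worth correcting, because planned size is a basic fact of the trial and the section that should fix it gives the wrong value.

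**What to change.** Reword the end of the Sample size calculation section to say that, after allowing for 15 % loss, 9501 patients per group are needed; that this is met with 48 clusters of 200 patients (9600 patients) per group; and that the trial therefore comprises 96 clusters and 19,200 patients in total. The text then agrees with the Abstract. The cost is a change of wording in two adjacent sentences. Recruitment, randomisation and analysis are unaffected.
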